#### Adverse event reporting, safety and criteria for discontinuing.

In this study, a non-standard treatment that is not currently implemented will not be evaluated. Consequently, side effects and adverse events will be documented as part of the routine monitoring process. However, the steering committee (TB, AEC) will assess interim analyses regarding any safety measures every six months. The study will be terminated if a new treatment relevant to patient groups in rectal cancer management is introduced during the study period and included in the guidelines, and/or there are unacceptable disease-free survival or local recurrence rates (a difference of more than 10%) in any treatment arm that could adversely affect the success of the project. To ensure the safe conduct of the project in the event of such risks, measures will be taken and monitored by the steering committee. The TSCRS will inform relevant parties and all members through e-mail, society website and social media accounts regarding important protocol amendments.

The study will continue until the necessary number of patients is reached. The study will be terminated if a new treatment relevant to patient groups in rectal cancer management is introduced during the study period and included in the guidelines, and/or there are unacceptable disease-free survival or local recurrence rates (a difference of more than 10%) in any treatment arm.

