### Sample size and recruitment

The literature reports a mean 3-year disease-free survival rate of 75–85% for the sample to be included in the study [16]. For patients with mid-rectal tumors (cT2N+ and cT3N0) without high risk MRI findings, the 3-year disease-free survival rate was estimated to be 80% for both direct TME and TME following neoadjuvant chemoradiotherapy. Under these conditions, with α = 0.05 (95% confidence interval) and 80% power, the power analysis indicated that a total of 396 patients (1:1 ratio) would be required. Considering a 10% dropout rate, it is planned to include 218 patients in each group, for a total of 436 patients.

According to data from the Turkish Ministry of Health, General Directorate of Public Health, a total of 24,312 patients were diagnosed with rectal cancer between 2020 and 2024, of whom 17,896 underwent surgery (https://hsgm.saglik.gov.tr/tr/kanser.html). Since this study will be conducted nationally under the sponsorship of the main society of Turkish colorectal surgeons TSCRS, we anticipate reaching the targeted patient number within five years from the start of the study. To achieve this goal, TSCRS will utilize various channels, including mailing, social media, and its website, to announce the study and inform surgeons about the protocol.

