### The data monitoring committee and interim analyses

Two members of the steering committee (TB, AEC) are responsible for data monitoring. These investigators will coordinate with the data processing secretary employed by the sponsor (TSCRS) to check the reliability and completeness of the data on a weekly basis. They will present reports to the steering committee every month and to the participant investigators twice a year. They are responsible for interim analysis and adverse event monitoring every six months.

The interim results of the study will be shared at national and international meetings and conferences as the primary and secondary endpoints are reached (in 1, 3 and 5 years after intervention). After completion of the study, the results will be prepared as a manuscript and published in a journal as well as clinicaltirals.gov.

The data monitoring committee members are affiliated with the sponsor, TSCRS, which is a non-profit professional association, and all investigators who are going to be invited in this study are members of this association. An independent monitoring committee has not been established for the study.

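### The 10% termination criterion, assessed every six months, has no precision requirement and no defined estimator, comparator or direction, so its false-stop probability is uncontrolled

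*Protocol article*

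**What the plan says.** The section on adverse event reporting, safety and criteria for discontinuing gives the termination rule twice. Both statements say that the study will end if "there are unacceptable disease-free survival or local recurrence rates (a difference of more than 10%) in any treatment arm". The first continues with "that could adversely affect the success of the project" and adds that the steering committee will take and monitor measures. The second, in the closing paragraph of that section, has neither addition.

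The section on the data monitoring committee and interim analyses sets the frequency. Of the two steering committee members in charge of data monitoring it says: "They are responsible for interim analysis and adverse event monitoring every six months". It also says: "An independent monitoring committee has not been established for the study". Participating investigators receive reports twice a year, and "The interim results of the study will be shared at national and international meetings and conferences as the primary and secondary endpoints are reached", at 1, 3 and 5 years after intervention.

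The planning assumption, under Sample size and recruitment, is that "the 3-year disease-free survival rate was estimated to be 80% for both direct TME and TME following neoadjuvant chemoradiotherapy".

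**The concern.** The rule has a number and a look schedule but nothing that says how precisely the difference must be known. Early on, few patients have follow-up, and a gap of 10 points between two equally good strategies is ordinary sampling variation. Repeated looks give that variation several chances to cross the line.

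The groups are also not randomised. The Statistical methods section adjusts the primary analysis by propensity score, and the Limitations section accepts that residual confounding may persist. The stopping rule mentions no adjustment, so a difference in case mix could trigger it.

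At stake is early termination of a study of equal strategies, leaving an overstated difference in the literature. There is a related risk. Treatment is chosen in routine care, so any between-group interim results shown to surgeons who are still recruiting could change who receives nCRT, and with it the groups being compared.

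**Working it through.** **Inputs from the protocol article.** 3-year DFS is 80% in both groups. There are 198 evaluable patients per group (396 in total) and 218 enrolled per group (436). Looks are six-monthly: 5 / 0.5 = 10 looks in five years and 8 / 0.5 = 16 in eight. The threshold is 10%. Accrual is expected within five years. The primary outcome section defines DFS as a proportion at three years after surgery.

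**Assumptions.** Accrual is uniform over five years, or over two as a faster case. DFS is exponential with hazard -ln(0.80)/3 = 0.074 per year in both groups. There is no dropout, and follow-up runs from entry. The 10% is read as 10 percentage points between groups, in either direction, and is applied as a numerical trigger.

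**The plan's own figure.** The article gives no operating characteristic for the stopping rule; its only related figure is the sample size, "with α = 0.05 (95% confidence interval) and 80% power". A non-inferiority calculation with a 10-point margin and one-sided alpha of 0.05 gives

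n per group = (1.645 + 0.842)² × 2 × 0.80 × 0.20 / 0.10² = 6.18 × 0.32 / 0.01 ≈ 198, total 396.

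This matches "a total of 396 patients (1:1 ratio) would be required". Then 198 × 1.10 ≈ 218 per group. The margin and the one-sided alpha are inferred, since the article states neither. A two-sided comparison of 80% with 90% gives 398, which is nearly the same.

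**One look, equal groups.** SE = √(2 × 0.80 × 0.20 / n), and P(|difference| > 0.10) = 2 × [1 − Φ(0.10 / SE)].

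| Patients per group | SE | P(difference > 10 points) |
|---|---|---|
| 20 | 0.126 | 43% |
| 30 | 0.103 | 33% |
| 50 | 0.080 | 21% |
| 100 | 0.057 | 7.7% |
| 198 | 0.040 | 1.3% |

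With five-year accrual, 218 / 5 = 43.6 patients enter each group per year. At 3.5 years about 43.6 × 0.5 ≈ 22 per group have full three-year follow-up, so the first look at which a three-year proportion exists is close to the top row. With two-year accrual the number is 109 × 0.5 ≈ 55.

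**Repeated looks, by simulation.** Probability that the difference exceeds 10 points at any look when the strategies are equal:

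| Reading of the rule | 5-year accrual | 2-year accrual |
|---|---|---|
| 3-year completers, no minimum number | about 53% | about 24% |
| Kaplan-Meier at 3 years, once estimable | about 20% | about 4% |
| Crude event proportions | about 10% | about 3% |

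**Sensitivity.**
- For completers with five-year accrual, a minimum of 20 per group gives about 42–44%, 30 gives 32–33%, and 50 gives 18–21%. A minimum of 100, with looks to year 8, gives 9%.
- Counting only one direction roughly halves the completer and Kaplan-Meier figures.
- Measuring 10 points below the expected 80% in either group, instead of between groups, gives about 28–31% (completers, five-year accrual, minimum of 1–10 per group).
- The local recurrence limb adds at most about 5 points, at an assumed 5% three-year rate. The article gives no planning rate for it.

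Confounding is not modelled in any of these figures.

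**The case against.** The strongest reply is that this is not an automatic trigger. The rates must be judged unacceptable, the first statement adds a qualifier, and the steering committee assesses the data. That stands to a point: the figures above are conditional on numerical application. But the second statement drops the qualifier, and the only content given to the word unacceptable is the 10% itself.

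A reader might infer that chance alone would probably stop the study. The document does not support that. Only the more permissive readings exceed one half. Three-year completers do so with five-year accrual and few or no patients required per group, and faster accrual, a minimum sample or a single direction brings the figure well below. A figure near 80% can be produced by reading a three-year Kaplan-Meier value from the first look, but up to year 3 nobody has three years of follow-up, so it does not fit the protocol's endpoint.

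A reader might also infer that comparative interim results will be presented at meetings. The text says interim results, without saying whether they are by group. Nor does the article state a 10-point non-inferiority margin; it is inferred from 396.

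Finally, boundaries and minimum information often sit in an SAP that is not shown. Their absence alone would be no finding. Here, however, the protocol itself fixes a termination criterion with a number and a schedule, and states it in two ways.

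**Conclusion.** The point holds as a badly fixed rule with an uncontrolled false-stop probability, not as a prediction that the study will be stopped. With equal 80% 3-year DFS and 218 per group, that probability runs from about 3% to about 53% over the three readings and two accrual speeds tabulated. The completer reading, which is closest to the protocol's definition of the primary outcome, gives about 53% at five-year accrual and about 24% at two-year accrual. Even the 20% for Kaplan-Meier at three years with five-year accrual is high for ending a study of equal strategies.

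These figures rest on uniform accrual, exponential DFS, no dropout, both directions counted and numerical application of the rule. Unadjusted differences between non-randomised groups could add to them. The change should be made, and it can be made before recruitment, which the article says has not started.

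**What to change.** 1. Reconcile the two statements of the rule so that there is one.
2. Keep the sponsor's 10-point difference as a trigger for committee review. State the estimator, the time point, the comparator (other group or expected rate) and the direction.
3. Allow termination for outcome only when a pre-set boundary that allows for repeated looks is crossed on the confounding-adjusted three-year difference. Haybittle-Peto or a spending function are examples. Require a stated minimum number of patients per group with three-year follow-up.
4. State that any between-group interim results are withheld from meetings and from participating investigators until recruitment has closed and the primary analysis is done.

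The cost is rewording the stopping paragraphs, the dissemination sentence and the sentence on reports to investigators. The downside is a slightly later reaction to an early unadjusted gap, which the review trigger in item 2 partly offsets.

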## Discussion

In line with current recommendations, some surgeons perform upfront TME for patients with T2-3 node-positive mid-rectal cancer in the absence of MRF involvement. However, in these cases, the common approach is to administer neoadjuvant chemoradiotherapy. This study seeks to evaluate whether upfront TME achieves non-inferior 3-year disease-free survival compared to the standard.

### Limitations

The non-randomized, observational design introduces the potential for selection bias. Although propensity score methods will be used to minimize selection bias, residual confounding may persist. Our study is expected to span at least five years, which presents logistical challenges both in terms of patient recruitment and follow-up. By the end of this period, the relevance and generalizability of the results may be limited due to potential changes in clinical practice and evolving treatment standards.

Moreover, the trial’s reliance on MRI-based risk stratification may lead to variability in interpretations across different centers, particularly in the absence of centralized imaging review. Another limitation is the absence of central pathology review, which may impact the consistency of histopathological assessments. To minimize these limitations, standard MRI and pathology assessments have been published on the study website. Additionally, standardized MRI and pathology evaluation protocols were presented during a webinar organized for candidate participating centers. Furthermore, the TSCRS commits to providing central review and support in cases where centers require assistance with MDT, MRI, or pathology evaluations.

Unfortunately, MSI testing is not yet performed as a standard procedure in endoscopic pathology in Türkiye. Many centers offer it only as an additional test, which is time-consuming, often not covered by insurance, and results in extra costs for patients. Therefore, MSI is tested in endoscopic pathology only if it is routinely performed at the center or if the patient consents to undergo testing at another institution at an additional cost. For this reason, we could not specify unknown pre-treatment MSI status as an exclusion criterion. However, MSI testing is routinely performed in final surgical pathology in our country. Patients found to have MSI positivity in surgical pathology will not be included in the final analysis. Similarly, patients who underwent preoperative MSI testing (if performed), were found positive, and/or received immunotherapy will also be excluded from the final analysis.

### Strengths

The CANO trial presents several notable strengths that contribute to its potential impact on clinical practice and the broader colorectal cancer literature. First, the study’s prospective, multicenter design involving numerous institutions across Türkiye ensures a high level of external validity and generalizability. By enrolling a large cohort of patients, the trial will provide robust statistical power. Additionally, the study’s observational nature reflects real-world practice, which enhances the applicability of the findings to routine clinical settings.

Another key strength is the rigorous inclusion and exclusion criteria based on MRI-based risk stratification, which aligns with contemporary guidelines advocating for personalized treatment strategies. The comprehensive data collection process, including both oncologic outcomes and patient-reported quality of life measures such as the LARS score and New Cleveland Clinic Colorectal Cancer Quality of Life Questionnaire, allows for a holistic evaluation of treatment efficacy and its impact on patients’ well-being.

The study’s voluntary, society-led approach fosters national collaboration among colorectal surgeons, potentially establishing a valuable model for future multicenter research initiatives in Türkiye. The transparent protocol submission and early feedback collection from the scientific community further strengthen the study’s methodological rigor.

## Conclusion

The CANO trial has the potential to provide pivotal evidence on the selective use of nCRT in mid-rectal cancer. If successful, the results could guide a more personalized approach to rectal cancer treatment, minimizing overtreatment without compromising oncologic outcomes. The study’s findings will not only contribute to the literature but also serve as a model for future collaborative research efforts in Türkiye and beyond.
